### Randomization and stratification

Random group allocation occurs a minimum of four weeks after inclusion and after rescreening. If eligible, permuted block randomization is performed. Randomization is stratified on the adjunct use of preventive medication.

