### Statistical analysis

Research hypothesis

The primary endpoint is to investigate the change in the mean number of migraine days from baseline to the last 28-day period in the treatment group compared with the wait-list control group. Thus, the null hypothesis (H0) and alternative hypothesis (H1) to be tested in relation to the primary objective are as follows.
•H0: The change in the mean number of migraine days from the 28-day baseline to the last 28-day period in the treatment group is equal to the change in the mean number of migraine days from baseline to the last 28-day period in the wait-list control group.

vs.
•H1: The change in the mean number of migraine days from the 28-day baseline to the last 28-day period in the treatment group is not equal to the change in the mean number of migraine days from baseline to the last 28-day period in the wait-list control group.

Sample size

The sample size calculation is based on an assumption of the effect size derived from a relevant meta-analysis of the efficacy of biofeedback in treating migraine
^
15
^ and a randomized pilot study.
^
9
^ Provided an effect size of d = 0.4, a significance level alpha of 0.05 (two-sided), power 0.8, and a dropout rate of 30% in the post-randomization period, the required sample size of this study was estimated to 286 participants. The anticipation of high dropout rates in this study is justified in the significant challenge of maintaining participant adherence observed in home-based mHealth studies.
^
9
^
^,^
^
16
^

Protocol deviations

Participants with incomplete or missing headache diary entries in more than 30% of days in the post-randomization period, participants with more than 30% missing or incomplete biofeedback sessions in the treatment arm, and participants initiating new or altering the use of their established preventive headache medications during the trial, are considered protocol deviators.

Statistical analysis plan

The statistical analysis plan (SAP) will include a technical and detailed description of statistical analysis. Statistical analyses will be conducted by an independent statistician. The analysis will follow a predefined order, where the primary efficacy endpoint is analyzed first. The trial statistician will analyze the efficacy outcomes without knowledge of treatment allocation by using a dataset with study arm allocation coded as groups A and B.

Data analysis set

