For the efficacy analysis, the full analysis set includes all randomized participants and constitutes the intention-to-treat (ITT) population. The per protocol (PP) population includes all randomized participants without protocol deviations.

Analysis dataset 1 is defined as the data from the 16-week period for all randomized participants and does not include extension period data. The 12-week post-randomization period in the biofeedback arm starts on the date of the first biofeedback session. Data lock for the evaluation of efficacy endpoints can be performed upon the completion of this dataset.

The safety data set includes all participants exposed to the biofeedback device.

Primary endpoint analysis

Analysis of the study endpoints will be performed in the ITT (all randomized subjects) and PP populations.

The primary endpoint variable is migraine days. The operational definition used for the analysis will be prespecified in the SAP.

The planned analysis strategy involves a mixed logistic regression model which will include all available daily eDiary entries. The mixed logistic regression model will be used to estimate the difference in the change from baseline in the mean number of migraine days per 28-day period between the treatment and waitlist groups. The model will include the presence or absence of migraine on each day from the baseline and 12-weeks post randomization periods as a dependent binary variable, treatment allocation, time period (baseline, week 1-4, week 5-8 and week 9-12) and an interaction term between treatment allocation and post-randomisation time-periods are included as categorical fixed effects, together with the stratification variable (concomitant preventive medication use). The patient ID will be included as a random effect. The site of inclusion will also be assessed as a potential random effect prior to the unblinding of the statistician to the treatment allocation. The model does not require explicit imputation, as mixed models yield unbiased estimates under the assumption that data are missing at random. This assumption will be assessed and sensitivity analyses considered if warranted.

The primary effect estimate will be the model-based estimates of the difference in change from baseline in mean monthly migraine days between the treatment and waitlist groups, presented with a 95% confidence interval.

Baseline variables that are considered to be highly predictive of outcomes will be discussed and identified

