*a priori* and described in the SAP. These variables will be included in multivariate analysis. The SAP will also detail the analysis strategies for the secondary outcomes. Post hoc stratified analyses by sex (women vs. men) and assessment of sex interaction will be conducted.

The statistical analysis plan includes predefined sensitivity analyses, restricting the primary analysis to the per-protocol set and, if feasible, subgroup analyses according to adherence status. Specifically:
•Participants in the interventional group with >90% biofeedback adherence in all three 28-day periods will be compared with the remaining participants in the interventional arm with lower adherence.•Participants in the interventional group with >90% adherence during weeks 1–4 will be compared with the remaining participants in the interventional arm with lower adherence in that same period.

Safety data

Safety objectives will be assessed by collecting data on treatment-emergent adverse events encountered during biofeedback training, including adverse events (AEs), serious adverse events (SAEs), adverse device effects (ADEs), serious adverse device effects (SADEs), and unanticipated SADEs (USADEs), and by evaluating the frequency and severity of these occurrences.

All data on treatment-emergent adverse events, ADEs, SADEs, and USADEs will be categorized and summarized. The frequency and severity of treatment-emergent AEs, ADEs, SADEs, and USADEs will be summarized for all enrolled participants and the entire duration of the intervention. Adverse events occurring more than once in individual participants will also be summarized and presented descriptively.

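### Entered only as a time-constant term, the stratification variable cannot adjust the primary contrast for a difference in change between preventive users and non-users; a term by time period would

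*Protocol article*

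**What the plan says.** Protocol article, Randomization and stratification: "Randomization is stratified on the adjunct use of preventive medication".

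Protocol article, Statistical analysis (Primary endpoint analysis): the outcome is migraine yes or no on each day, from baseline through week 12. The fixed effects are arm, a four-level time period that includes baseline, and arm by post-randomisation period, "together with the stratification variable (concomitant preventive medication use"). Patient is a random effect. Arm by period is the only interaction named. The primary estimate is the between-arm difference in change from baseline in monthly migraine days. The section argues that no imputation is needed, because mixed models are unbiased when data are missing at random.

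Baseline variables judged highly predictive are left to the SAP, and of these the article says: "These variables will be included in multivariate analysis". It does not say in what form they enter.

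The sample size section assumes "a dropout rate of 30% in the post-randomization period".

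**The concern.** A stratification factor is normally put in the model so that the treatment contrast is adjusted for it. Here the contrast is a difference in change, and a time-constant term does not touch change. If preventive users and non-users follow different courses over the 12 weeks, nothing in the stated model represents that.

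This bears on the missing-data argument. Likelihood estimation is valid under missing at random only if the mean model is right. Suppose dropout depends on arm and stratum, and the stratum predicts change. The data are then missing at random given variables already in the model, yet the estimate is biased because the stratum's own trend is left out.

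Unequal dropout between arms is plausible. Only the treatment arm is asked for daily sessions, and the Discussion reports session adherence falling from 80% to 20% in the feasibility study. Adherence is not dropout, however, and the article gives no dropout figure by arm or by stratum.

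**Working it through.** **Inputs from the protocol.** d = 0.4, two-sided alpha 0.05, power 0.8, dropout 30%, N = 286; model terms as described above.

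**The plan's own figure.** The normal formula gives 2 × (1.960 + 0.842)² / 0.4² = 98.1, so 99 per arm. The t-test gives 100 per arm. With 1:1 allocation (assumed), 200 / 0.7 = 285.7, so 286, which reproduces "the required sample size of this study was estimated to 286 participants". No covariate enters that calculation, so this point does not affect it.

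**Algebra.** For patient i in period t, with arm A, stratum S and random intercept u, the plan's model is

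logit p(i,t) = β + αA(i) + π(t) + δ(t)A(i) + γS(i) + u(i).

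The change from baseline to weeks 9–12 is π(9–12) − π(baseline) + δ(9–12)A(i). Both γS(i) and u(i) are gone, and the difference between arms is δ(9–12). This is exact on the logit scale and needs no numerical assumption. In days the cancellation is only approximate, because the logit link is non-linear.

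If the truth also contains λ(t)S(i), the planned model's δ is shifted by roughly λ(9–12) × (share of preventive users among biofeedback patients still observed − the same share on the waitlist). Stratified allocation makes that bracket close to zero unless dropout differs by arm and stratum.

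**Hand check.** Assume 30% preventive users and λ = 0.3. Assume biofeedback-arm dropout of 45% in non-users and 15% in users, and 20% on the waitlist. User share among those remaining on biofeedback: 0.30 × 0.85 / (0.30 × 0.85 + 0.70 × 0.55) = 0.255 / 0.640 = 0.398. Waitlist share: 0.30. Shift ≈ 0.3 × 0.098 = 0.03 log-odds. Average dropout is (36% + 20%) / 2 = 28%, close to the plan's 30%.

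**Simulation, set 1.** 60 trials of 286 patients per scenario. Assumed: 30% preventive users, random-intercept SD 0.6, random-change SD 0.4, baseline log-odds −1.1, true effect −0.35, stratum effect 0.5 on level and 0 or 0.4 on change. Entries are the weeks 9–12 contrast in log-odds, then in days (model SE).

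| Scenario | No stratum term | As planned | With stratum × period |
|---|---|---|---|
| Balanced, stratum affects level only | −0.336; −1.640 (0.432) | −0.336; −1.637 (0.432) | −0.336; −1.636 (0.432) |
| Balanced, stratum also predicts change | −0.336; −1.721 (0.438) | −0.335; −1.716 (0.437) | −0.338; −1.707 (0.436) |
| Dropout differs by arm and stratum, stratum predicts change | −0.409; −2.081 (0.436) | −0.392; −1.994 (0.435) | −0.351; −1.766 (0.439) |
| Forced 65/35 imbalance, stratum predicts change | −0.268; −1.389 (0.438) | −0.268; −1.361 (0.436) | −0.347; −1.745 (0.445) |

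The third row is the extreme case: 0.041 / 0.351 = 12%, or 1.994 − 1.766 = 0.23 days. The fourth row shows the mechanism only; stratified allocation would not be expected to produce it.

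**Simulation, set 2.** 400 trials, true effect −0.25 (about 1.3 days), patient SD 0.5, change SD 0.4, stratum difference in trend 0.3, dropout as in the hand check. Planned −0.213 against −0.234 with the period term: 0.021 / 0.234 = 9%, and 0.021 × 1.3 / 0.25 = 0.11 days. With the dropout pattern reversed, −0.247 against −0.233: 6%, 0.07 days, the other way. The complete-data value is about −0.233.

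**Simulation, set 3.** True effect −0.35. With complete data, −0.3386 without the stratum term and −0.3387 with it. With complete data or uniform 30% dropout, the period term moves the estimate by 0.003 to 0.007 (SD 0.08 to 0.10). With dropout related to arm and stratum: moderate −0.325 against −0.337 (0.012, 4%); strong −0.331 against −0.354 (0.023, 6%). At set 1's ratio of 1.766 / 0.351 ≈ 5 days per log-odds, these are 0.06 and 0.12 days.

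**Other covariates, if entered in the same form.** In set 2's setting with complete data, a level term moved the contrast by 0.0001 to 0.0002. Entry by period cut its variance by 4% (covariate predicting 0.15 log-odds of change per SD) or 13% (0.25 per SD).

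**The case against.** The strongest reply is that the design already handles this factor. Permuted-block randomisation stratified on preventive use balances it, and the second table row shows that even a stratum that predicts change then costs nothing visible (SE 0.437 against 0.436 days). Bias needs two conditions together, a different trend in preventive users and dropout that differs by arm and stratum, and the article documents neither. Even the extreme 0.23 days is about half the model SE of 0.44. The article also promises to assess the missing-at-random assumption and to consider sensitivity analyses. All of this stands, and it limits the size of the point. It does not make the term effective where adjustment would be needed, and an assessment of missing at random would not by itself reveal an omitted stratum trend.

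A reader might infer more than the documents support:

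- **That the primary result is unadjusted for the stratification factor.** Level differences between strata are removed by the within-patient contrast and the random intercept. Only a difference in change is left.
- **That the term has no effect at all.** Cancellation is exact only on the logit scale. Under unequal dropout, including the term moved the estimate by about 0.09 days (−2.081 to −1.994).
- **That precision is being lost on this factor.** The balanced scenarios show no gain to recover. The 4 to 13% variance figures belong to other, assumed covariates.
- **That every predictive variable must move into the primary model.** The article leaves the choice and form of those variables to the SAP, so that part is conditional.

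**Conclusion.** The point holds in a limited form. As stated, the model does not adjust for a difference in change between preventive users and non-users; on the logit scale this follows from the model alone. With complete data, or dropout unrelated to arm and stratum, the consequence is negligible. If preventive users change differently and dropout differs by arm and stratum, the primary estimate is off by roughly 4 to 10% of the effect, reaching 12% in the most extreme scenario. That is about 0.05 to 0.2 days per 28, with the sign set by the dropout pattern. The sizes rest on assumed values for the share of preventive users, the trend difference, the dropout rates and the patient-level variation, none of which the article gives. The simulated means also carry Monte Carlo error: in set 1, about 0.11 / √60 = 0.014 log-odds. Comparisons between models fitted to the same data are more reliable than the distance of either from the true value. The change is still worth making, because it costs almost nothing and supports the missing-at-random argument on which the plan relies.

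**What to change.** In Primary endpoint analysis, list preventive-medication use by time period among the fixed effects, next to its main effect. Time period has four levels, so this adds three parameters. When the model is converted to days, average both arms' predictions over the same mix of users and non-users. If the SAP adds predictive baseline variables to this model, say there that each enters with its term by period, since level terms alone would nearly reproduce the unadjusted result.

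The cost is one sentence, settled before the statistician is unblinded. No new data are needed and N is unchanged. The standard error rises very slightly (0.435 to 0.439 days, about 1%, in the unequal-dropout scenario). There is little gain if preventive use does not predict change.

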### Study intervention

Investigational medical device

The medical device Cerebri consists of a smartphone app and a set of two wireless non-invasive sensors. Both sensors are skin-contact-dependent. One sensor is attached to the index finger and measures HRV and peripheral skin temperature. The second sensor is attached to the skin over the upper trapezius muscle fibers using adhesive electrodes and measures muscle tension as surface electromyographic voltage (
Figure 2A and
2B). The sensors transmit the measurements to the user’s smartphone by Bluetooth technology and display them in real time to the user. Participants receive the sensors by mail together with a brief written onboarding guide. All training is delivered in a standardised, app-based format without individualised or therapist-led instruction. The app guides users through the first three biofeedback sessions, and provides a library with textual instructions on exercises that the user can choose to use in their biofeedback training. By following instructions for suggested exercises displayed in the Cerebri smartphone app, the subject trains on influencing the measured parameters in the desired direction during each biofeedback session.
Figure 3A-C illustrate how visualization of the physiological measures is displayed on their smartphone. Exercises to facilitate successful manipulation of the physiological parameters include breathing techniques, progressive muscle relaxation, and awareness training. A visual breathing pacer to support paced breathing is available in the mobile app to the user during the entire treatment session. It is desirable to increase HRV and peripheral skin temperature and lower neck muscle tension. Participants are instructed to sit comfortably in a quiet room during treatment. Throughout the intervention period, participants are required to complete a 10-minute biofeedback session at least once daily at a time of their choosing. They have the option to perform as many as six sessions each day.

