^ to be both feasible and acceptable for app-based biofeedback. The non-invasiveness of the Cerebri-system is advantageous in several ways. First, it enables the patients to safely perform the procedure themselves. Second, it means the risk profile is relatively low, with the most severe identified risks being electrical failure in the sensors or charger, skin contact-dependent allergic reactions from the sensor material, and risks related to information security and privacy. All the identified risks were met using an appropriate mitigation strategy. Third, a wider spectrum of patients qualifies for study inclusion; notably, women of childbearing potential who do not use highly effective contraceptives, as well as those who are pregnant or breastfeeding.

The BioCer trial is not blinded and employs a waitlist control. In a previous sham-controlled trial involving adolescents that tested an earlier version of the Cerebri system, the investigators encountered difficulties in developing a biofeedback sham that effectively imitated authentic biofeedback.
^
9
^ False feedback was easily detected by the user, compromising the integrity of the blinding protocol. Conversely, attempts to distort the biofeedback signal by introducing minor “errors” resulted in a sham signal that was “too similar” to true biofeedback, potentially inducing a treatment effect. In addition to the practical challenge of developing an appropriate sham signal, there are significant ethical concerns associated with providing false biofeedback to participants. These concerns include the potential exacerbation of migraines. Indeed, in theory, introducing a false biofeedback signal could lead to mislearning, in which subjects inadvertently adapt incorrect or maladaptive responses based on what they believe to be true biofeedback. Nevertheless, the absence of blinding is a limitation, as it prevents assessment of the placebo effect.

We believe that the effectiveness of Cerebri depends on achieving adequate user satisfaction and adherence to ensure optimal results. However, a recurrent challenge for smartphone-based biofeedback is its low adherence. A pilot study in adolescents of a progenitor version of Cerebri reported poor adherence, with a mere 40% of planned biofeedback sessions completed during weeks 5-8 of the study.
^
8

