^ Similar adherence challenges have been reported for smartphone-based systems. In the feasibility study of the current Cerebri system proceeding this trial, biofeedback adherence was also low, declining from 80% in week 1-4 to 20% in week 9-12.
^
11
^ Several usability and software issues were identified and addressed before trial initiation.

To improve the usability of the Cerebri mobile app, additional data were added to the diary and visualized in graphs to provide users with better tools to keep track of their headaches and to compare headache data with biofeedback data directly. In addition, the app content was revised and instructions were improved based on reported use errors or misinterpretations. Based on user insights, the app interface during the biofeedback sessions was tailored to ensure that the biofeedback was performed correctly. Furthermore, the algorithm for calculating the HRV score was modified to compensate for drifting biofeedback scores resulting from frequency leakage from the low-to high-frequency domains of the HR wave. Some drifting still occurs, but it is deemed acceptable as the users are considered unable to observe this.

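### The adherence comparison that requires more than 90% in all three periods will probably be too thin to inform; adherence on its full scale should be the main supportive analysis

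*Protocol article*

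**What the plan says.** Under Statistical analysis (Primary endpoint analysis), the protocol article lists sensitivity analyses that include, "if feasible, subgroup analyses according to adherence status". Two are specified, both within the biofeedback arm and both split at the same level:

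- All periods: "Participants in the interventional group with >90% biofeedback adherence in all three 28-day periods will be compared with the remaining participants" of that arm.
- Early period: "Participants in the interventional group with >90% adherence during weeks 1–4 will be compared with the remaining participants" of that arm, over the same four weeks.

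The section Study intervention sets the denominator: "participants are required to complete a 10-minute biofeedback session at least once daily at a time of their choosing". No reason is given for 90%.

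The Discussion reports earlier experience. In the feasibility study of the current system, "biofeedback adherence was also low, declining from 80% in week 1-4 to 20% in week 9-12". In an adolescent pilot of a progenitor version the figure was "a mere 40% of planned biofeedback sessions completed during weeks 5-8 of the study". The Discussion adds: "Several usability and software issues were identified and addressed before trial initiation".

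**The concern.** Session adherence over a period is a count: 0 to 28 per 28-day period and 0 to 84 overall, if one session a day is required. Both analyses reduce it to two classes, and the first makes the upper class hard to enter because a participant must clear the cut three times. The lower class then mixes near-complete users with people who did no sessions.

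The Discussion says the sponsor believes that effectiveness depends on adequate adherence, and these are the within-arm analyses the article sets out on that question. If the upper group is small, the all-periods comparison is either not run, with no fallback stated in the article, or gives a wide interval around no difference. The latter could be taken as evidence that adherence does not matter.

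**Working it through.** **Inputs.** From the sample size paragraph: d = 0.4, two-sided alpha 0.05, power 0.8, dropout 30%, N = 286. From the Discussion: mean adherence 80% in weeks 1-4 and 20% in weeks 9-12. Assumptions: 1:1 allocation (the ratio is not stated), hence 143 in the biofeedback arm, or 100 after 30% dropout; one required session a day.

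**The plan's own figure.** A two-sample t-test with these inputs needs 99.08, so 100 per arm; 200/0.7 = 285.7, which rounds up to 286. The sample size reproduces.

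**What the cut means.** 25/28 = 89.3% and 26/28 = 92.9%, so passing needs at least 26 of 28 days in each period.

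**Ceiling on the upper group.** If the mean in weeks 9-12 is 20%, the share at or above 26/28 cannot exceed 0.20/(26/28) = 21.5%, or 0.215 × 143 ≈ 31 people. That needs everyone else to do nothing in weeks 9-12. No more can pass in all three periods together.

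**Detectable difference.** d = 2.80 × √(1/k + 1/(n − k)), with k the number above the cut. The last column is the power for a difference of 0.4, Φ(0.4/√(1/k + 1/(n − k)) − 1.96), for illustration.

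| Share above cut | k of 143 | Detectable d at 80% power | Power if d = 0.4 |
|---|---|---|---|
| 5% | 7.15 | 1.07 | 18% |
| 10% | 14.3 | 0.78 | 30% |
| 21.5% (ceiling) | 30.8 | 0.57 | 50% |

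Whole participants (7 v 136, 14 v 129) give 1.09 and 0.79. A cap of 0.20/0.90 = 22.2% gives 0.56. With 100 in the arm, 5% and 10% give 1.29 and 0.93, with power 14% and 22%.

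**Weeks 1-4.** With a mean of 80% the split need not be extreme. Assumed shares of 30-60% above the cut give 59-67% power for d = 0.4 with 143, and 45-52% with 100.

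**Full scale against cut.** Simulation, all assumptions mine: benefit proportional to sessions done and averaging d = 0.4; beta-distributed adherence with mean 80% in weeks 1-4, falling linearly to 20%, 40% or 60% in weeks 9-12; concentration 1.5 (wide spread) or 4 (narrow); between-period correlation 0.7; n = 100 or 143.

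| Analysis | Power, >90% cut | Power, full scale |
|---|---|---|
| All periods, wide spread | 3-14% | 26-61% |
| All periods, narrow spread | 0-9% | 17-37% |
| Weeks 1-4 | 8-23% | 14-36% |

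Repeat runs moved these limits by about three points at most. The gain is about 9 to 54 points for the all-periods analysis and 5 to 14 for weeks 1-4.

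**The case against.** **The feasibility figures do not show that almost nobody exceeds 90%.** A reader might infer that, but the Discussion gives aggregate figures without a distribution. Up to about a fifth could pass with a mean of 20%. A more all-or-nothing spread (concentration 0.5) puts about 7%, 17% and 31% above the cut in all periods for weeks 9-12 means of 20%, 40% and 60%. This stands: the small group is likely, not established.

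**Adherence may be better in the trial.** Usability issues were addressed beforehand, and the Data collection section adds adherence calls and a dashboard for contacting low adherers. This also stands. Even so, in the simulated scenarios with proportional benefit the full-scale analysis did better at a weeks 9-12 mean of 60% too.

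**The gain depends on the assumed shape.** Proportional benefit favours a linear term. If benefit of 0.8 SD appears only above the cut, the ranking reverses: with a 60% weeks 9-12 mean, wide spread and n = 143, the cut had about 91% power against 35% for the linear term, and a repeat run gave the same ranking. For the same reason d = 0.4 is a yardstick and not a forecast of the within-arm difference. This is why the >90% comparison should be kept in a secondary place.

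**Feasibility condition and unseen plan.** The wording allows a hopeless comparison to be skipped, but that leaves the question unanswered. The full statistical analysis plan may hold other adherence analyses, so it cannot be said that these two are the only ones.

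**Different thresholds.** The protocol-deviation limit concerns "participants with more than 30% missing or incomplete biofeedback sessions in the treatment arm". A deviation limit and a high-adherence subgroup serve different purposes, so the difference from 90% is no defect.

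**Conclusion.** The point holds as a low-cost improvement to a supportive analysis. On the protocol's own feasibility mean, the all-periods comparison has an upper group of at most about 31 of 143 and a detectable difference of at least about d = 0.57, rising to 1.07 if 5% pass. It also discards the variation below the cut. This rests on 1:1 allocation, one required session a day, and late adherence near the feasibility level, which is a warning only.

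Two stronger readings are not supported. It does not follow that both adherence analyses are near-powerless: the weeks 1-4 split may be close to balanced, and its gain from the full scale is modest. Nor does the point touch the trial's conclusion: these are non-randomised comparisons within one arm, and the primary intention-to-treat analysis and the sample size of 286 are unaffected.

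**What to change.** Make the main adherence analysis in the biofeedback arm one that uses the proportion of required daily sessions completed, over 84 days and, separately, over weeks 1-4. Enter it as a continuous covariate interacting with time period in the mixed logistic model already planned. Report the model-based change in monthly migraine days per 10 percentage points of adherence with a 95% confidence interval, labelled associational because adherence is not randomised. Check the shape with a spline. Keep the two >90% comparisons as secondary or descriptive, with the number of participants in each group.

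The cost is wording in the analysis plan and an added model term; no new data or participants are needed. The downside is that a dose-response form is assumed, and a linear term would have less power than the cut if benefit appears only above a high threshold. The spline and the retained comparison cover that case in part.
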